#### CRCEI and Health Session Participant Eligibility Criteria

Youth aged ≥13 years and adults who speak English and live within the identified neighborhoods are eligible to participate. Individuals can participate in the CRCEI or Health Sessions without participating in the research procedures.

Individual participants in the intervention training and the comparison health sessions are sampled by availability. Comparison and intervention sites use the network of community partners identified in the asset maps created for each neighborhood. This includes site leaders, program facilitators, recruiters with strong connections to their community, prevention specialists embedded in schools, and tabling at community outreach events. In the intervention sites, the research team also works collaboratively with community partners and facilitators, as well as community residents and organizations engaged in phase I of the intervention to recruit youth and adult residents to participate in the training. In addition, each community partner staff and resident community facilitator personally identifies and recruits residents in their personal and professional networks. Participant recruitment started in February 2023 and continued until the eighth neighborhood completed enrollment, through November 2024.

Individual youth and adult participants in the community survey are sampled randomly and by availability. In the first 2 intervention neighborhoods, availability sampling that primarily relied on facilitator recruitment did not yield adequate response rates and raised concerns about sampling bias. The team then adapted the data collection strategy and moved toward random sampling, adapting the Centers for Disease Control and Prevention’s CASPER model [38]. A dataset of residential addresses from county parcel, address, and property assessment data was assembled, and 30 residential addresses were randomly selected [39], their related US Census blocks were extracted, and those blocks were used to survey each of the 8 participating neighborhoods. The research team canvasses door to door, inviting participation in the community survey from each residence within each selected block. The number of blocks across the 8 neighborhoods ranges from 12 to 28 blocks. The number of addresses per neighborhood ranges from 524 to 2403. Given time limitations to the team’s ability to visit addresses multiple times, inability to reach some residents at home, and underrecruitment of community survey participants, random sampling is supplemented with recruitment of participants in public areas and community events (ie, availability sampling).

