## Methods

### CRCEI (Experimental) and Health Sessions (Comparison) Arms

#### CRCEI (Experimental Arm)

As discussed earlier, the CRCEI takes place across 3 phases. In phase I (approximately 3 mo), *community mobilization and engagement* takes place. Researchers identify and partner with a community-based organization in each neighborhood whose mission, goals, and programs align with the intervention. The community partner and other community organizations help to identify 3 residents as community facilitators. This phase includes conducting a community analysis, a baseline community survey, and community engagement activities, attending community events and engaging with and getting feedback on the intervention from community residents and organizations. It also includes preparing the community partner and facilitators for the training, including reviewing and adapting training facilitation guides and case scenarios for role plays and other activities for each neighborhood, and recruiting youth and adult residents to attend the training.

Phase II is the *collective efficacy training*, which includes 9 training sessions over approximately 10 weeks (including a 1-wk break). The training location, dates, and times are discussed and decided with community partners and facilitators. The training sessions are held in accessible community locations, and dinner is provided at the beginning of each session. The youth present and get feedback on their community project ideas in the last session, and community resources are invited to share information and listen to the youth’s ideas. A community project planning committee is also formed in the last session.

In phase III (approximately 4 to 6 mo), the community partner and facilitators work with the community project planning committee to further develop and implement *a community project*. Each community receives a US $5000 grant to implement the project, which focuses on increasing collective efficacy and social connections, using intervening skills to take action on issues identified by participants in the training, providing alternatives to violence, particularly for young people, and increasing community resources. The project, selected by the community members, may include youth-centered community events and tangible products (eg, rehabilitation of recreational spaces) for young people and the wider community.

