#### Evaluation Design

The CRCEI was initially funded by the Substance Abuse and Mental Health Services Administration as part of a broader effort across the county to promote community mental health and increase resiliency. Subsequently, the team also received research funding from the Centers for Disease Control and Prevention to conduct a rigorous evaluation of this intervention (a cluster randomized controlled trial across similar neighborhoods is ongoing). As CRCEI was already being implemented in several neighborhoods to assess impact, a quasi-experimental matched comparison group design was used, using participatory propensity score matching to identify comparison neighborhoods with similar baseline characteristics as the sites already implementing CRCEI. Four neighborhoods receiving the CRCEI intervention are compared with 4 propensity-matched neighborhoods receiving the comparison health sessions. The study uses a community-based participatory and partnered approach. For this reason, we offered an alternative intervention in comparison communities rather than “care as usual” or “no intervention” to promote reciprocity. Furthermore, our aim was to match the demographics and characteristics of the communities and use the same data collection methods and measures in the intervention and comparison communities to analyze the aims for this study.

As illustrated in Figure 2, survey data were collected from participants in the intervention and comparison groups at 3 time points: baseline (T1; prior to exposure to the training or health sessions), post training or health sessions (T2; immediately following the 9-wk CRCEI training or last health session), and follow-up (T3; approximately 6 mo after the T2 to coincide with the completion of phase III in the intervention arm). To address secondary aims and inform neighborhood adaptation of the CRCEI, community survey data are collected at baseline (T1) and follow-up (T3), and secondary data on community and youth violence incidence are measured annually. In addition, an ethnographic process evaluation, including implementation science frameworks, is conducted to elucidate how CRCEI is implemented across intervention neighborhoods [31,32]. The evaluation focuses on dimensions of fidelity, reach, dosage, responsiveness, differentiation or characteristics, and adaptation and draws on a mix of observation, feedback questionnaires, and attendance, interview, and secondary data.

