#### Secondary Outcome Measures

The evaluation has 2 groups of secondary outcomes, those at the participant level and those at the neighborhood level. Intermediary, individual-level beliefs and behaviors related to collective efficacy are measured, including participants’ willingness to intervene, social connections, and prointervening norms and values. *Willingness to intervene* is a modified version of the Collective Efficacy social control subscale, with questions focusing on whether the participant is likely to intervene in social problems (ie, in lieu of whether they perceive their neighbors as being willing to intervene) [36]. *Social connections* are measured via 3 questions asking how many neighbors (youth and adults) that participants know by sight, name, and talking to on a regular basis (range 0 to >10). *Community norms, values and attitudes about intervening* is a scale asking participants the degree to which they agree with 10 statements related to norms and values pertaining to intervening in social problems [10]. *Exposure to violence* [37] is measured using 17 items with binary yes or no response options, including 9 items capturing *direct exposure* to violence and 8 items capturing *indirect exposure* to violence (ie, witnessing violence). This exposure to violence measure has been previously validated [37]. Exposure to violence values are calculated by the proportion of respondents endorsing each item (ie, responding “yes”). These data are collected from residents in the intervention and comparison neighborhoods via the community survey and at 2 time points, baseline and follow-up.

At the neighborhood level, we measure *collective efficacy* using the same measure of collective efficacy described earlier [26], which is aggregated to a mean value based on responses among all participants within a given neighborhood on the community survey. Prior research uses self-reported survey measures to measure collective efficacy at the individual and neighborhood levels. We measured collective efficacy at the individual level by surveying participants in the intervention and comparison sessions. We also measured collective efficacy at the neighborhood level through our community survey, and similar to Sampson et al, the responses are aggregated to the neighborhood level.

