#### Aim 2 (Neighborhood-Level Outcomes)

The neighborhood is the unit of analysis. The dependent variables are neighborhood-aggregated outcomes (eg, mean collective efficacy scores and rates of crime or violence). The independent variable is treatment assignment. The primary analysis will use an analysis of covariance specification, where the neighborhood-level outcome at follow-up is regressed on treatment assignment and the baseline value of the same outcome. This model provides an adjusted mean difference in follow-up outcomes between intervention and comparison neighborhoods, controlling for baseline heterogeneity. As only 8 clusters are available, models will not include random effects but will instead rely on cluster-robust variance estimators with small-sample corrections. Adjustment for additional neighborhood-level covariates (eg, baseline socioeconomic disadvantage, racial composition, and baseline crime levels) will be included cautiously in sensitivity analyses, given the limited degrees of freedom. These covariates will be added one at a time to assess the robustness of the primary results. Sensitivity analyses will also include difference-in-differences models, where the dependent variable is the change from baseline to follow-up. Results will be expressed as standardized effect sizes for comparability across outcomes and to provide planning parameters for future trials.

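### The community survey apparently changed sampling method between baseline and follow-up in 2 of the 4 intervention neighborhoods only, and the survey-based Aim 2 models can mistake that change for a treatment effect

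*Protocol article*

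**What the plan says.** The sampling of the community survey is described under CRCEI and Health Session Participant Eligibility Criteria. It starts with availability sampling: "In the first 2 intervention neighborhoods, availability sampling that primarily relied on facilitator recruitment did not yield adequate response rates". The same sentence says that this raised a worry about sampling bias. "The team then adapted the data collection strategy and moved toward random sampling": residential addresses were drawn at random, their census blocks were identified, and "those blocks were used to survey each of the 8 participating neighborhoods". Because recruitment still fell short, "random sampling is supplemented with recruitment of participants in public areas and community events (ie, availability sampling").

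On timing, CRCEI (Experimental Arm) says of Phase I: "This phase includes conducting a community analysis, a baseline community survey, and community engagement activities". Evaluation Design gives the community survey two waves, T1 and T3.

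On analysis, Secondary Outcome Measures defines neighborhood collective efficacy as the survey score "aggregated to a mean value based on responses among all participants within a given neighborhood on the community survey". The primary model under Aim 2 (Neighborhood-Level Outcomes) is an ANCOVA in which "the neighborhood-level outcome at follow-up is regressed on treatment assignment and the baseline value of the same outcome". A difference-in-differences model on the change from baseline is listed as a sensitivity analysis. The additional covariates named there are all neighborhood-level: disadvantage, racial composition and baseline crime.

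**The concern.** Residents reached through a facilitator's network may differ from residents reached at a randomly chosen block in how they rate trust and informal control among neighbors. If the first two intervention neighborhoods have a T1 mean built mainly on facilitator recruits and a T3 mean built on block canvassing plus a supplement, part of their T1-to-T3 change is a change in who was asked. The early facilitator-led phase is reported only for intervention neighborhoods, so this part is aligned with arm. Both planned models take the T1 mean at face value, and no stated analysis uses recruitment mode.

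The direction is not known. If facilitator recruits rate collective efficacy higher, baseline is inflated and the CRCEI effect is understated. If they rate it lower, the effect is overstated. Analytic Approach puts the emphasis on magnitude rather than on significance, and Aim 2 offers its standardized effects as planning parameters for later trials, so a biased point estimate matters even when the test is not significant.

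**Working it through.** **1. Which wave is affected.** The sampling paragraph names no wave. Three facts point to T1:
- The first community survey in an intervention neighborhood is the Phase I baseline.
- The only other wave is T3.
- Results dates the first community surveys to 9 September 2022, before the evaluation funding of 1 October 2022, and says the four intervention sites were already participating before that grant.

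This is a strong inference, not a statement. A repeated or topped-up T1 in those two neighborhoods is not excluded.

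**2. The plan's own scale.** Sample Size and Power states baseline-adjusted detectable effects of 1.9, 1.7, 1.4 and 1.2 at r = 0.60, 0.70, 0.80 and 0.85. With 4 versus 4 neighborhoods, df = 6 and 80% power (stated for Aim 1, assumed here for Aim 2):

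MDES = [t(0.975, 6) + t(0.80, 6)] × √(1/4 + 1/4) × √(1 − r²) = 3.353 × 0.707 × √(1 − r²)

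This gives 1.90, 1.69, 1.42 and 1.25, so the stated figures reproduce in units of the neighborhood-level SD.

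**3. How a baseline shift enters.** Let b be the shift that the sampling method adds to the T1 mean of the two affected neighborhoods, in neighborhood SD, with no true treatment effect.
- The intervention-arm T1 mean moves by (2/4) × b = b/2. The comparison-arm mean does not move.
- Difference-in-differences: the contrast of changes moves by −b/2.
- ANCOVA: the adjusted difference subtracts slope × (difference in T1 means). With slope about r, it moves by about −r·b/2.

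**4. Simulation check.** Eight neighborhoods, 8,000 runs per setting, no treatment effect; ANCOVA by ordinary least squares (df 5), difference-in-differences with df 6. With b = 0 the mean estimates lay between −0.006 and 0.013.

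| b | ANCOVA, r = 0.80 | −r·b/2 | Diff-in-diff, r = 0.80 | −b/2 |
|---|---|---|---|---|
| 0.25 | −0.100 | −0.100 | −0.125 | −0.125 |
| 0.50 | −0.192 | −0.200 | −0.249 | −0.250 |
| 1.00 | −0.330 | −0.400 | −0.490 | −0.500 |

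The ANCOVA formula slightly overstates the bias at larger b, because the shift also weakens the fitted slope. At b = 1.0 and r = 0.80, false rejection at the nominal 5% level was 7.0% for ANCOVA and 8.9% for difference-in-differences. A negative b reverses every sign.

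**5. What b might be.** The protocol gives no figure. As an illustration, assume that facilitator recruits differ by 0.2 to 0.4 individual SD and that each neighborhood-wave has 50 respondents. The SD of a neighborhood mean is √(ICC + (1 − ICC)/50), which is 0.263 at ICC 0.05 and 0.465 at ICC 0.20. The arm-level shift is 0.1 to 0.2 individual SD.
- Difference-in-differences: 0.38 to 0.76 at ICC 0.05; 0.22 to 0.43 at ICC 0.20.
- ANCOVA with slope 0.7: 0.27 to 0.53; 0.15 to 0.30.

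Sampling after the switch is itself a mixture of random and availability recruitment, so the gap between the two waves could be smaller than assumed.

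**6. Precision of the exclusion analysis.** Dropping the two neighborhoods leaves 2 versus 4. By the same method, df = 4 and MDES at r = 0.70 is (2.776 + 0.941) × √(1/2 + 1/4) × √(1 − 0.49) = 3.717 × 0.866 × 0.714 = 2.30, against 1.69 with all eight.

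**The case against.** The strongest reply is that the text does not establish the problem as fact. A reader might infer that the baseline in these two neighborhoods was availability-only and that follow-up was purely random. The document supports neither. It names no wave, it says only that sampling relied mainly on facilitators, and it says that availability recruitment continued after the switch. That limits the claim to an apparent change from mainly facilitator-recruited to mixed sampling. It does not remove the point, because a topped-up T1 would still mix methods, and facilitator sampling at both waves would sit badly with the statement that the blocks were used in all eight neighborhoods.

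A reader might also infer that all of Aim 2, or the trial's main result, is affected. It is not. Police-recorded violence does not depend on the survey, and the primary outcome comes from the participant survey.

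Third, the assumed bias is below the stated detectable effects of 1.2 to 1.9. That stands for significance testing, much less for estimation.

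Finally, an article may leave sensitivity analyses to an SAP that is not shown. But this article itself fixes the all-respondent mean and the use of T1 in both models. The limitation on availability sampling in the Discussion concerns session participants, not this switch.

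**Conclusion.** The point holds for survey-based Aim 2 outcomes. If the affected wave is T1, as the study sequence suggests, an arm-aligned change of sampling method enters the treatment contrast at about b/2 for difference-in-differences and r·b/2 for ANCOVA, and neither model removes it. The sign is unknown. The size rests wholly on an assumed b; the gap of 0.2 to 0.4 SD and the 50 respondents per neighborhood-wave are illustrations, not document figures. Difference-in-differences carries the larger bias, so agreement between the two models would be no reassurance on this point. This concerns a secondary outcome and can be repaired with data already collected, provided that recruitment mode can be recovered.

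**What to change.** 1. State, for each of the eight neighborhoods, which sampling method supplied T1 and which supplied T3. If T1 in the first two was repeated or topped up, say so.
2. Flag each community-survey record as facilitator, random canvass or public/event recruitment wherever this can be recovered.
3. Add to Aim 2, for survey-based outcomes only: (a) a T3 comparison restricted to random-canvass respondents that does not use the affected T1 means; (b) the ANCOVA and difference-in-differences models without the two affected neighborhoods.
4. Interpret the main estimate in light of (a) and (b), and say that the full-sample difference-in-differences is not a check on this bias.

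A pooled regression adjustment for recruitment mode is tempting but should not be used. The availability recruitment described after the switch is in public areas and at events, not through facilitators. The facilitator effect is therefore confounded with the T1 wave of those two neighborhoods and could absorb part of the treatment effect.

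Cost: wording and data coding, with no new data collection if mode is on record. Table 3 lists survey tracking forms, but only as a source for households invited, so recovery is not assured. Analysis (a) gives up baseline adjustment in a non-randomized comparison. Analysis (b) has a detectable effect of about 2.3 at r = 0.70. Both will have wide intervals, so they supplement the primary model and do not replace it. Results dates the start of analysis to April 2026, so the date on which they are added should be recorded.

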### Ethical Considerations

For the intervention and comparison groups, youth receive a description of the research study and a parental letter about the study. The parent letter includes an option for parents or caregivers to decline their child’s participation. The study was approved by the University of Pittsburgh Institutional Review Board (STUDY221001093). The Institutional Review Board approved a waiver of parental permission and a waiver of signed written consent. Research assistants (RAs) review the verbal consent form with participants at the beginning of the first intervention training and comparison health sessions and answer any questions pertaining to confidentiality, the program flow, and survey time points. The consent form covers all 3 waves of data collection, T1 through T3 as described earlier. For the community survey, verbal consent is obtained from all youth and adult participants.

### Retention in Program and Research

Once youth and adults are recruited, retention throughout the program is a key focus. Upon enrolling in either the comparison or experimental arm, prospective participants receive program information and complete a contact information sheet. RAs ensure that the document is legible and that all fields are completed. RAs use this information to contact the participant prior to each session to remind them of the session. Retention in the program is also promoted by compensating participants US $25 for attending each session. In the intervention sites, an additional US $25 is provided if participants attend all training sessions. New participants cannot enroll in the intervention training sessions after session 2.

Retention for participant survey data collection is facilitated by collecting detailed contact information and offering incentives for survey completion (US $25 for T1, US $25 for T2, and US $25 for T3; see Figure 2 for study flow). Participation in T2 and T3 surveys is facilitated via tracking participants with the help of community organizations that host the health sessions in the comparison sites and community partners and facilitators in the intervention sites. Participants provide detailed contact information at baseline to facilitate follow-up. Contact information is confirmed again at sessions following the baseline survey and at the T2 survey. Participants are also called or texted periodically by RAs between follow-up surveys to ensure that contact information is still valid. Finally, for those who miss a survey in the appropriate time frame, a comprehensive “make-up” survey is offered (with the same monetary compensation) to update contact information and increase the likelihood that they will participate in the next survey.

